#### Study Setting

The study is based at the Murdoch Children’s Research Institute (MCRI) at the Royal Children’s Hospital in Parkville, Melbourne, VIC.

#### Eligibility Criteria

Participants were eligible if they did not meet the exclusion criteria and could attend a Saturday workshop at the Royal Children’s Hospital between weeks 26 and 29 of gestation.

#### Exclusion Criteria

To ensure practicality, participants were excluded if they were aged under 18 years, not in control of their diet (including choice of foods purchased and meals eaten), were uncomfortable communicating in English, or resided further than 1 hour’s travel from the Hospital. To ensure suitability of the dietary intervention, participants were excluded if they had a clinically diagnosed bowel condition or were on a medically advised exclusion or restriction diet. To assess intervention efficacy, participants needed to be free of conditions that may alter their gut microbiota. Hence, participants must not have had any of the following: a body mass index of 30 or greater; diabetes mellitus (type 1, 2, or gestational diabetes); a clinical diagnosis of a current mental illness (including major depression, dysthymia, anxiety disorder, social phobia, posttraumatic stress disorder, obsessive compulsive disorder, panic disorder, an eating disorder [anorexia, bulimia, and binge-eating disorder]), psychotic disorder (schizophrenia), substance use disorder, autism disorder, attention deficit hyperactivity disorder, attention deficit disorder; or used antibiotics or probiotic supplements in the previous month; or regularly use illicit drugs.

#### Sample Size and Power

The study was powered to detect a between-group difference in alpha diversity (Shannon index) in infants. At design time in 2015, very few studies reported infant alpha diversity measured at 4 weeks, and no studies that we are aware of have ever reported differences in infant alpha diversity as a function of a maternal dietary intervention; thus, it was difficult to estimate an expected change. Instead, a clinically relevant difference in Shannon index was determined based upon the small number of case-control studies reporting differences between the Shannon index of healthy 4-week old infants to those with health problems (such as allergy) [2,4,27]. Across these studies, the mean between-group difference in Shannon index ranged between 0.2 and 0.3. Standard deviations were derived for each group ranging between 0.2 and 0.5, with 0.4 being most common. On the basis of these data, the sample size was calculated using the power.*t* test function of the R *stats* package (R Core Team, version 3.2.0). A sample of 80 mothers would provide 80% power to detect a difference in Shannon index of at least 0.25, assuming a standard deviation of 0.4 and a 2-sided type I error of 0.05. Therefore, 90 pregnant women would be recruited to participate, this permitted a loss to follow-up of 10 participants (12.5%).

### Recruitment

Melbourne-based women were recruited online or within the community (obstetric clinics, doctor’s surgeries, maternal and child health centers, childcare, playgroups, toy libraries, shopping centers, physiotherapy centers, sports centers, and radio). Online recruitment strategies included pregnancy forums, twitter, and paid Facebook advertisements that targeted Melbourne-based women aged between 18 and 40 years who met Facebook pregnancy-related demographic characteristics.

### Randomization

The randomization process used a concealed 1:1 group allocation ratio with randomly permuted block sizes to ensure allocation was unpredictable. External personnel prepared the randomization schedule and applied it to the Research Electronic Data Capture (REDCap) randomization module [28]. The study administrator used REDCap to randomly allocate each participant. After allocation, blinding was no longer possible because the team had to book study visits or a workshop.

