### Objectives

The Healthy Parents, Healthy Kids (HPHK) study (Trial registration: Australian New Zealand Clinical Trials Registry, ACTRN12616000936426) is a prospectively registered open-label, parallel group, RCT of an educational perinatal dietary intervention targeting gut microbiota from the third trimester of pregnancy until 4 weeks after birth. The primary aim is to evaluate whether the dietary intervention alters alpha diversity of the infant gut microbiota 4 weeks after birth. Secondary aims are to evaluate the efficacy of the intervention in altering microbiota, inflammatory and stress profiles, epigenetic regulation, and maternal diet and well-being. The feasibility and acceptability of the study intervention will also be evaluated. The HPHK study intervention design couples pedagogical theory and educational design (focused on self-assessment and self-efficacy) with Behavior Change Techniques (BCTs) [21] to support efficacy and dietary adherence. A sound educational design is an important, yet seemingly overlooked consideration; first, it ensures that participants are able to *do* the target behavior, second, it helps to mitigate against confusing a true null effect with insufficient learning, and third, it safeguards the literature against spurious findings from poorly designed interventions.

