### Data and Sample Collection

Data were collected at 4 time points: gestation week 26, 31, 36, and 4 weeks after birth (follow-up), as detailed in Table 1. Data collection included demographic, physical health and medications, mental health and social support, diet, lifestyle, and evaluative feedback. A probiotic food and drink questionnaire was administered at all time points for the intervention group, but only at baseline and follow-up for the control group to prevent the control group from becoming aware or prompted to increase intake of probiotic foods.

The study team were trained to collect baseline and follow-up anthropometrics and biological samples. Biological samples were collected as outlined in Table 2. Participants collected a baseline stool sample during gestation week 26, and a follow-up sample from themselves and their infant 4 weeks after birth. Stool samples were stored in the domestic freezer and transported on ice to the study visit scheduled during week 26 of gestation (or before week 29). The study team collected the follow-up samples during a home visit. Samples were transported to long-term storage (−80°C) on dry ice. At the conclusion of the study, stool samples were couriered on dry ice to the Australian Genomic Research Facility (AGRF) for DNA extraction and 16S rRNA sequencing. The V3-V4 hypervariable region of the 16S rRNA gene was amplified using a forward primer, 341F, 5’-CCTAYGGGRBGCASCAG-3’ and reverse primer, 806R, 5'-GGACTACNNGGGTATCTAAT-3'. Polymerase chain reaction amplicons were generated from approximately 100 ng of extracted DNA, and purified amplicons were sequenced using Illumina MiSeq, in accordance with the manufacturer specification and AGRF protocols.

**Table 1 table1:** Data collection schedule.

Measurement/instrument		Baseline (gestation week 26; mother)	Progress (gestation weeks 31 and 36; mother)	Follow-up (4 weeks postpartum)	
				Mother	Infant

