### Data Management and Access

Questionnaires were administered electronically to participants through REDCap [28], which is hosted on secure servers at MCRI. Information is kept confidential through a secure password-protected system and restrictive user-access permissions. Study team access to participant information was strictly limited to the purposes of running the study, such as organizing study visits, support calls, and recording biological sample collection. For analysis, the investigators have access to the final deidentified trial dataset.

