#### Secondary Outcomes

#### Gut Microbiota

Infant stool alpha diversity will be further analyzed using 4 other measures (Inverse Simpson, Chao1, phylogenic diversity, and observed species) using the same methods described for the primary outcome. All 5 alpha diversity measures will be analyzed for mothers adjusting for baseline measures. Further analyses will examine potential effect modification for storage duration, baseline, antibiotic, and medication use in accordance with Kraemer et al [54]. Between-group differences in the relative abundance of genus *Prevotella* will be analyzed using the same methods described for the primary outcome for infants and a baseline-adjusted method for the mothers.

A total of 2 beta diversity metrics will be calculated (Generalized UniFrac distances [55] and Bray-Curtis dissimilarity.) Group-based separation will be visually inspected using principal coordinates analysis and constrained ordination plots of these beta diversity metrics. Further plots will be created to inspect separation based on potential effect modifiers: mode of birth, antibiotics, sample collection week, and mode of feeding. Permutational multivariate analysis of variance (PERMANOVA) [56] with 999 permutations will be used on the beta diversity metrics to determine the statistical significance of group-based separation. In a secondary analysis, these PERMANOVA models will test for the aforementioned potential effect modifiers. Differential abundance testing with a false discovery rate correction will be performed to explore OTUs that are different between groups. The appropriate transformation and test will be determined in accordance with Weiss et al once library size is known [57]. For significant outcomes, the role of dietary change or probiotic or prebiotic supplementation in potentially mediating microbial outcomes will be examined.

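### The article rules out all blinding after allocation for a reason that covers only the booking staff; sequence processing and analysis can still be masked, and it should say whether they and the laboratory were

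*Protocol article*

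**What the plan says.** Objectives describes a study that "is a prospectively registered open-label, parallel group, RCT of an educational perinatal dietary intervention". Under Randomization, external personnel prepare the schedule and load it into REDCap. Then: "The study administrator used REDCap to randomly allocate each participant". The next sentence is the only statement on blinding: "After allocation, blinding was no longer possible because the team had to book study visits or a workshop".

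The route of the primary outcome is described elsewhere:

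- **Collection** (Data and Sample Collection): "The study team collected the follow-up samples during a home visit".
- **Laboratory** (same section): after the study had ended, "stool samples were couriered on dry ice to the Australian Genomic Research Facility (AGRF) for DNA extraction and 16S rRNA sequencing". This is told in the past tense. Sample labels, and whether they showed the arm, are not mentioned.
- **Data access** (Data Management and Access): "For analysis, the investigators have access to the final deidentified trial dataset".
- **Analysis set** (Statistical Methods): modified intention to treat, requiring at least one postbaseline follow-up that is valid.
- **Primary test** (Primary Outcome): Student t test or Wilcoxon-Mann-Whitney, according to a visual reading of quantile-quantile plots.
- **OTU testing** (Gut Microbiota): "The appropriate transformation and test will be determined in accordance with Weiss et al once library size is known".

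**The concern.** The reason given does not support the breadth of the conclusion. Booking a workshop unmasks the person who books it, and participants know whether they attended one. Neither fact reaches an outside sequencing facility, the person who turns reads into a Shannon value, or the person who runs the test.

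In an open-label trial whose primary endpoint is a laboratory measure, these later steps are where masking remains possible. Several decisions there are left until the data are in hand. If the person deciding can see the arms, a choice can lean, knowingly or not, toward the directional hypothesis of higher diversity with the intervention. The Discussion says the overall effect will be unbiased because the design is randomized. Randomization balances the groups at allocation; it gives no protection against choices made afterwards with the arm in view.

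**Working it through.** No figure in the article rests on the blinding sentence, so the main check sets the passages against each other.

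**1. Whom does the stated reason cover?**

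| Step | Who | Does booking visits or workshops reveal the arm? |
|---|---|---|
| Allocation, bookings | Study administrator and team | Yes |
| Workshop, support calls | Facilitators, participants | Yes, by the nature of the intervention |
| Follow-up stool collection | Study team, at home | Possibly; same team |
| DNA extraction, 16S sequencing | Separate facility, after the study | No |
| Sequence processing, Shannon index | Not named | No |
| Statistical analysis | Investigators, deidentified data | Not through bookings, unless the same people booked |

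The reason covers the first two rows and perhaps the third. The sentence claims all six.

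**2. Does deidentified mean masked?** No. Removing identity does not remove the arm. Table 1 also marks the progress-visit probiotic questionnaire, the workshop evaluation and the personal goals as collected in the intervention group only. A file holding those fields shows the arm even with the allocation column deleted. Whether the file used for the stool analysis holds them is not stated.

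**3. Which choices remain open, and what do they touch?**

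- Validity of a follow-up: decides who is analyzed, so it touches the primary outcome.
- Reading the quantile-quantile plots: decides the primary test.
- Transformation and test once library size is known: touches only the exploratory OTU comparison, which carries a false discovery rate correction.

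**4. Would masking change the design figures?** Inputs from Sample Size and Power: difference 0.25, SD 0.4, two-sided alpha 0.05, power 80%, 80 evaluable; 1:1 allocation from Randomization.

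- Normal approximation: n per arm = 2 × (1.960 + 0.842)² × 0.4² / 0.25² = 2 × 7.85 × 2.56 ≈ 40.2, rounded up to 41, or 82 in total. Power at 40 per arm is 79.8%.
- t-based: 41.17 per arm, rounded up to 42, or 84 in total. Power at 40 per arm is 78.8%.

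The stated 80 is reproduced to within rounding. Masking alters none of these inputs, so no sample-size figure changes.

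**5. Size of any bias.** This would need the number of discretionary decisions, their direction and whether the decider knew the arm. The article gives none of these, so no estimate is possible.

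**The case against.** The strongest defense is that the sentence sits under Randomization, directly after the allocation step, and only explains why staff and participants were unblinded in a trial already called open-label. On that reading the article is merely silent on laboratory and analyst masking, which a condensed article may leave to the full protocol or analysis plan. Part of this stands: the absence of detail on sample codes and batch layout is not in itself a fault. But the article is not silent on blinding. It says blinding was not possible, without limit, and gives a reason that cannot carry that statement.

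Three stronger readings are tempting and are not supported.

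- *The laboratory and analysts worked unmasked.* Nothing says so. Sequencing was off site and samples may have been coded.
- *The bias is a sizeable share of the target effect.* One can build a case: dropping one infant 2 SD (0.8) from an arm mean of 40 moves that mean by 0.8/39 = 0.021, or 8% of 0.25; three such exclusions move it by 3 × 0.8/37 = 0.065, or 26%. This assumes extreme samples, arm-aware exclusion and a common direction, none of which is in the article. Against a standard error of 0.4 × √(2/40) = 0.089, one such exclusion is about 0.23 standard errors. It shows what selection could do, not what this plan does.
- *The OTU choice threatens the primary endpoint.* It does not; it governs exploratory testing and is tied to a cited method.

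It is also fair that Shannon diversity from sequencing is a largely objective measure, so the bench is a smaller worry than the analysis, and that coding and batch mixing can no longer be changed if sequencing is complete.

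**Conclusion.** The point holds as an over-broad statement with a practical consequence. The article declares blinding impossible for a reason limited to the coordinating team, while its own workflow leaves sequence processing and statistical analysis open to masking. If those steps were masked, the sentence is inaccurate and undersells the trial; if they were not, an avoidable risk remains. Either way it should change.

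The size of any bias cannot be determined, and no sample-size figure is affected. The conclusion assumes that the future tense of Statistical Methods is accurate, so that validity, processing and test-choice decisions were still ahead, and that the past-tense account of sequencing means the laboratory work was finished. It does not depend on anyone having known the arm. This is a free improvement, not a defect that undermines the trial.

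**What to change.** 1. Reword the Randomization sentence so that it applies to participants, workshop and call facilitators, and the coordinating team.
2. Decide sample validity and exclusion and complete sequence processing on data with the arm removed, leaving out the fields that Table 1 marks as intervention group only.
3. Choose the primary test, and the OTU transformation and test, with arms removed or recoded A/B, the code being held by the external personnel who prepared the schedule. An A/B code hides direction, but a two-sided P value is the same whichever label is which. So record each choice before any between-arm test is run.
4. Run the primary analysis under the A/B code and unmask only once these decisions are locked and dated.
5. For sequencing already done, report whether the laboratory was masked and how the arms were distributed across extraction and sequencing batches. If any step in 2 to 4 has already been taken with the arm visible, say so.

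Cost: a recoded variable, a short dated record of decisions, and a few sentences of text. No extra participants, samples or staff are needed.

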### Participation

As a gesture of appreciation, participants received an Aus $20 grocery store gift voucher at the initial study visit. In recognition of effort, completed participants entered a raffle to win an Apple iPad, this was drawn at the end of the study. When the study results are known, participants will receive a summary of results and an invitation to attend a presentation.

### Intervention

The objectives of the dietary intervention were that participants become educated, motivated, empowered, and equipped with the skills and self-efficacy to make long-term dietary change targeting the gut microbiota. The gut microbiota were targeted as the intervention’s change mechanism, and the target behavior was *eating for the gut microbiota*. We expected that the intervention would be feasible and accepted because when asked about support preferences, pregnant women wanted nutrition education, preferably in person and individually tailored [18,29].

#### Intervention Procedures

Participants attended a dietary workshop between gestation weeks 26 and 29. Participants devised and agreed upon 3 personalized dietary goals, and they received 2 support calls to encourage adherence. Intervention procedures are detailed in Multimedia Appendix 3. For intervention fidelity, each workshop and support call followed a predefined facilitator script to ensure that all participants received the same information.

#### Dietary Recommendations

The intervention aimed to align participants’ diets to the Australian Dietary Guidelines [25], and increase intakes of fibrous plant-based foods, while reducing intakes of highly refined and processed foods. Common probiotic species (*Lactobacillus* and *Bifidobacterium*) are reported to be safe during pregnancy [30], and perinatal probiotic supplementation may increase Bifidobacterial species in infants [11]. The intervention took a sustainable, *whole of diet approach* where prebiotic- and probiotic-containing food sources were recommended to participants instead of using supplements. This *synbiotic* combination of prebiotic and probiotic foods may help to promote the growth of probiotic species [31].

#### Educational Design

The educational design used the theory of constructive alignment [32], which argues that alignment among intended learning outcomes, learning activities, and assessment is crucial for learning. Clear learning outcomes were developed for the workshop (Multimedia Appendix 4) using the Structure of Observed Learning Outcomes taxonomy [33], which allows targeting particular levels of functioning with respect to knowledge. Learning activities were designed to provide opportunities for learners to practice the particular learning outcomes; this aligns with constructive alignment’s focus on what learners do rather than on what educators do. Participants engaged in active learning tasks like problem solving, which have been shown to be more effective for learning than transmissive or *lecture* style teaching [34]. At an educational psychology level, learning activities were designed with consideration of cognitive load theory [35] to manage the demands on participants’ working memory; this was deployed through chunking content, provision of reference materials, and careful use of different media. The workshop focused on developing participants’ ability to make judgments about their diet quality. The ability to self-assess is crucial for long-term retention and application of knowledge beyond the workshop [36], as participants need to be able to judge the quality of their diet to improve it. An expert in educational design and pedagogy reviewed the workshop materials. The logic model in Multimedia Appendix 4 details how the educational design, monitoring, feedback activities, and BCTs were used in the intervention.

#### Behavior Change Techniques

To support adherence, the intervention used BCTs [21]. Behavior change is an effective method for supporting dietary adherence in community-based interventions [37-39], including among pregnant populations [40]. Successful dietary BCTs include social support [37,38], information [40], instruction [39,40], self-monitoring [39,40], self-efficacy [38], goal-setting [37,39], goal review [39], relapse prevention techniques [39], motivational interviewing [39,40], feedback provision [39], and rewards (if goals are met) [40]. Descriptions of the intervention’s use of Michie et al’s BCTs [21] are available in Multimedia Appendices 3 and 4.

### Control Group

Treatment as usual was used as an active control condition. Participants continued receiving dietary advice from a health care provider who was managing their pregnancy. The rationale for using treatment as usual was to be able to compare the intervention against standard treatment [41]. In addition, provision of a different treatment as an active control may have introduced factors that could have altered the gut microbiota or bias the results.

Participants from both groups reported on the dietary advice that they received from their health care provider. Both groups also reported on their dietary intake, including prebiotic and probiotic foods, and dietary supplements. All nonwithdrawn participants received the intervention materials in written form upon study closure after sample and data collection closed.

### Data and Sample Collection

Data were collected at 4 time points: gestation week 26, 31, 36, and 4 weeks after birth (follow-up), as detailed in Table 1. Data collection included demographic, physical health and medications, mental health and social support, diet, lifestyle, and evaluative feedback. A probiotic food and drink questionnaire was administered at all time points for the intervention group, but only at baseline and follow-up for the control group to prevent the control group from becoming aware or prompted to increase intake of probiotic foods.

The study team were trained to collect baseline and follow-up anthropometrics and biological samples. Biological samples were collected as outlined in Table 2. Participants collected a baseline stool sample during gestation week 26, and a follow-up sample from themselves and their infant 4 weeks after birth. Stool samples were stored in the domestic freezer and transported on ice to the study visit scheduled during week 26 of gestation (or before week 29). The study team collected the follow-up samples during a home visit. Samples were transported to long-term storage (−80°C) on dry ice. At the conclusion of the study, stool samples were couriered on dry ice to the Australian Genomic Research Facility (AGRF) for DNA extraction and 16S rRNA sequencing. The V3-V4 hypervariable region of the 16S rRNA gene was amplified using a forward primer, 341F, 5’-CCTAYGGGRBGCASCAG-3’ and reverse primer, 806R, 5'-GGACTACNNGGGTATCTAAT-3'. Polymerase chain reaction amplicons were generated from approximately 100 ng of extracted DNA, and purified amplicons were sequenced using Illumina MiSeq, in accordance with the manufacturer specification and AGRF protocols.

**Table 1 table1:** Data collection schedule.

Measurement/instrument		Baseline (gestation week 26; mother)	Progress (gestation weeks 31 and 36; mother)	Follow-up (4 weeks postpartum)	
				Mother	Infant
